#### Baseline measures

We will collect participants’ HPV vaccination status, socio-demographic information (date of birth, nationality, religion, habitual residence, economic status, parental employment and marital status, and family or friends’ cancer history), health and sexual history. We will also record information about knowledge, cognition and beliefs related to HPV and HPV vaccination, motivations and intentions to uptake the HPV vaccine, decision-making, self-efficacy and objective skills regarding HPV vaccination. For background information, we will refer to the relevant part of several related studies conducted in China previously. The 11-item scale from Kahn JA and the HAVIQ (HPV Adolescent Vaccine Intervention Questionnaire) from Forster AS will be partly used to measure knowledge about HPV and HPV vaccination [30, 31]. For measuring cognition of HPV infection and prevention, we will use scales from Kim HW, Gerend MA and Guvenc G [32–34]. This will assess the perceived severity of HPV infection and the perceived benefits and barriers of HPV vaccination. Two scales from Ralph will be used to measure the perceived susceptibility of HPV infection [35]. The 5-item scale from Gerend MA will be adopted to test the influence of subjective norms [33]. For measuring decision-making for health protection, we will use the 3-item scale of Forster AS [31]. Self-efficacy for completing the 3-dose HPV vaccination will be tested using the 4-item scale of Gerend MA [33]. The self-administered 4-item scale developed by Fisher will also be used to measure the objective skills needed to initiate and complete HPV vaccination [26]. Finally, intent to receive the HPV vaccine will be measured according to the answer to the question: “Willingness to take the HPV vaccine in the next 6 months”.

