### Sample size calculation

To date, no studies have investigated the effects of a mobile app-based intervention with Chinese female college students to improve the HPV vaccine uptake. For this reason, the anticipated effect size is largely based on findings derived from similar research literature in other countries. This study will apply a two-tail test with α = 0.05 and β = 0.20. Statistical power was originally calculated based on an absolute difference of 10% (20% of girls in the intervention group relative to 10% of girls in the control condition would initiate vaccination). The number of cases needed in each group of each sub-center is 119 as calculated by Statistical Analysis System (SAS) V.12. Allowing for a 20% rate of loss to follow-up, 240 cases are required in each group, and a total of 480 cases are required for each trial center. Consequently, this study requires a total of at least 3360 participants in 7 schools.

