### Statistical analysis

Since the study collects data through electronic questionnaires, there will be no formal data monitoring committee. Participants fill out the questionnaire and automatically upload it to a read-only database to ensure the authenticity of the data; however, all data will be reviewed by the research team at regular intervals throughout the study.

We will conduct all analysis using IBM SPSS Statistics 22.0, Version 22.0. Data will be checked for internal consistency and logic prior to further analysis. An intention-to-treat analysis will be performed. Descriptive statistics of all variables will be calculated, including means and standard deviations or frequencies as appropriate. We will assess the potential bias in enrollment and follow-up by comparing characteristics using a Wilcoxon Rank Sum, chi-squared, or Fisher Exact test as appropriate.

Proportions of qualitative variables will be compared between the intervention and control groups using chi-squared tests at baseline and repeated at 1 month, 3 months and 6 months after intervention. For each of these measures, the change in proportion from the baseline to these 3 point-ends will be tested within intervention groups using McNemar’s tests. Unadjusted odds of vaccine uptake and intent to vaccinate for the intervention participants versus the control participants will be calculated using a logistic regression model. Bivariable and multivariable logistic regression models will be used to determine the independent effect of the intervention. Results of logistic regression models will be expressed as odds ratios (ORs) and 95% confidence intervals (95% CIs). Measures of acceptability and satisfaction for intervention participants will be summarized using counts and sample proportions. All final statistical tests are two sided with α = 0.05.

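### The planned McNemar tests of change from baseline within arm(s) do not estimate the intervention effect and should be dropped or labelled descriptive; the planned between-arm analyses stand

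*Protocol article*

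**What the plan says.** The Statistical analysis section of the protocol article sets out three layers of testing.

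- Between arms, unadjusted: "Proportions of qualitative variables will be compared between the intervention and control groups using chi-squared tests at baseline and repeated at 1 month" and at the two later visits.
- Within arm: for each of those measures, "the change in proportion from the baseline to these 3 point-ends will be tested within intervention groups using" McNemar's tests. The phrase can mean the intervention arm alone or each arm separately. No purpose is given and the tests are not called descriptive.
- Between arms, modelled: an unadjusted logistic model for uptake and intent, and then "Bivariable and multivariable logistic regression models will be used to determine the independent effect of the intervention". The covariates are not listed.

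The section closes with "All final statistical tests are two sided with α = 0.05", which covers the McNemar tests as well.

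The Abstract defines the primary outcome as a difference between the two groups. The Outcome measures section counts either a first dose received or an appointment for one. Baseline values exist for these measures. The Baseline section records vaccination status, and the Baseline measures section adds "We will also record information about knowledge, cognition and beliefs related to HPV and HPV vaccination", together with motivation and intent. The Sampling and randomization section places randomisation after this survey.

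**The concern.** A within-arm test asks whether a proportion changed over time. The trial asks whether it changed more with the education than without it. The control arm is there to remove what happens anyway: passage of time, answering the same questionnaire four times, and growing awareness of a vaccine that the Discussion describes as approved in China for only three years.

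For receipt of a dose the problem is sharper. A woman can move from unvaccinated to vaccinated but not back, so the direction of change is known in advance and the p-value depends only on how many women were newly vaccinated.

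What is at stake is how the results are reported. Because the tests are formal and unlabelled, a significant improvement from baseline could be presented as support for the intervention. The Discussion already reads an earlier school-based trial in this way. It cites a rise from 52.5% to 59% in the intervention group against no change in a control group at 60.9%, and concludes that such programmes promote vaccination. The rise is 6.5 points, yet the intervention group ends 1.9 points below control (60.9 − 59).

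**Working it through.** **Inputs from the protocol article**

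- Assumed rates (Sample size calculation): "20% of girls in the intervention group relative to 10% of girls in the control condition would initiate vaccination".
- Arm size: 240 per group per centre × 7 centres = 1,680; 1,680 × 2 = 3,360, which agrees with the stated total.
- Loss to follow-up of 20%: 1,680 × 0.8 = 1,344 per arm, if loss is equal in both arms (an assumption).
- Test level: 0.05, two-sided.

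The plan gives no figure for the McNemar tests themselves. Its per-centre figure of 119 is not reproduced by the usual pooled formula at 20% versus 10% with 80% power, which gives 199. That is a separate matter and is not used below.

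**Step 1: receipt of a first dose.** With b women newly vaccinated and no reversals, the exact two-sided McNemar p-value is 2 × 0.5^b.

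| b | Exact p | Continuity-corrected chi-squared p |
|---|---|---|
| 5 | 0.0625 | 0.074 |
| 6 | 0.031 | 0.041 |
| 7 | 0.016 | 0.023 |

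Six women are 6/1,680 = 0.36% of an arm, or 6/1,344 = 0.45% after loss.

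**Step 2: an untreated arm at the plan's own control rate.**

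- 10% of 1,680 is 168 women: p = 2 × 0.5^168, about 5e-51.
- 10% of 1,344 is about 134 women: p = 2 × 0.5^134, about 1e-40.

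**Step 3: significance is not automatic.** The binomial probability of at least six new vaccinees, over an assumed range of uptake:

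| Newly vaccinated | n = 1,680 | n = 240 (one centre) |
|---|---|---|
| 0.25% | 0.25 | < 0.001 |
| 0.5% | 0.84 | 0.001 |
| 1% | 0.999 | 0.03 |
| 2% | 1.00 | 0.35 |
| 5% | 1.00 | 0.98 |
| 10% | 1.00 | 1.00 |

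The test can therefore fail when early uptake is very low, or within a single centre.

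**Step 4: no intervention effect, both tests side by side.** Simulation with 4,000 runs, 1,680 per arm and the same uptake in both arms:

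| Scenario (baseline and lapse rates assumed) | McNemar significant, each arm | Between-arm test significant |
|---|---|---|
| 10% new uptake, none positive at baseline | 100% | 5.4% |
| 10% new uptake, 5% positive at baseline, half lapse | 100% | 5.1% |
| 5% new uptake, 5% positive at baseline, half lapse | 92% | 5.3% |

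The last two rows represent appointments that are not kept. The composite is then no longer one-way, but the within-arm test still rejects in most runs, while the between-arm test keeps its level.

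**Step 5: intent.** Assume 10% of women switch down and 10% plus a shift switch up, equally in both arms, so that the intervention does nothing. With n = 1,680, the within-arm test is significant in 4.7%, 39%, 98% and 100% of runs for shifts of 0, 2, 5 and 10 points.

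**Step 6: the between-arm test already planned.** At 20% versus 10% its power is above 99.9% with 1,680 or 1,344 per arm, and 86.8% with 240 per arm, treating women as independent.

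**The case against.** The strongest reply is that the protocol never rests efficacy on these tests. The primary outcome is a between-group difference, chi-squared tests compare the arms at every visit, and the independent effect of the intervention is explicitly assigned to logistic regression with odds ratios and confidence intervals. This stands, and it limits the point to uninformative supplementary tests.

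A reader might go further in four directions that the documents do not support.

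- That the vaccination tests must come out significant, or that one discordant cell must be empty. Only the direction is fixed, and only for doses received. The outcome also counts appointments, which can lapse, and significance still needs about six new vaccinees (Step 3).
- That no baseline-adjusted comparison will be made. The multivariable covariates are simply not listed. Baseline values are collected and may be among them, and a condensed article may leave the list to the full plan.
- That a method for scale scores is missing. The article states no wrong method for them, and its silence may likewise be filled by the full plan.
- That a McNemar test in the control arm is certainly planned. The wording may refer to the intervention arm alone. Step 2 shows what an untreated arm would give; it does not predict a table. If only the intervention arm is tested, its p-value would appear with no control change beside it, which is no better.

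The reply does not remove the core. The tests are formal, unlabelled and answer a different question from the trial's.

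**Conclusion.** The concern holds in a limited form. The within-arm McNemar tests at 1, 3 and 6 months cannot separate the intervention from time, repeated questioning or a secular trend. For first-dose receipt, about six new vaccinees suffice for p < 0.05, and at the plan's own 10% control rate an arm that received nothing would reach p of about 1e-40 (1,344 women, assuming equal 20% loss). The simulated results for lapsed appointments and for intent rest on assumed baseline, lapse and switching rates; they show the pattern and are not forecasts.

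The planned between-arm chi-squared and logistic analyses remain valid, so the primary comparison is not undermined. The risk is one of interpretation and reporting, and it can be removed before any data are seen.

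**What to change.** Amend the Statistical analysis section as follows.

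1. Delete the McNemar tests. Alternatively, present change from baseline descriptively for both arms side by side, with counts and proportions and no p-values.
2. State that every claim about the effect of the intervention rests on between-arm comparisons.
3. State that the planned logistic models for each visit include the baseline value of the same measure. For doses received, women already vaccinated at baseline cannot change and would be predicted perfectly by that covariate. The article does not list prior HPV vaccination as an exclusion, so say how these women are handled, for example by analysing women unvaccinated at baseline. Baseline status is recorded before randomisation, so this restriction keeps the arms comparable.

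The cost is a few sentences of analysis wording. No new data, visits or participants are needed, because the baseline values are already collected.

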## Discussion

Given that cervical cancer is one of the major causes of death among women worldwide, interventions to prevent high-risk types of HPV (HPV16 and HPV18) infection are urgently warranted. This study will be the first to evaluate whether a mobile-based approach combining theory-based education can improve HPV vaccination among females from mainland China.

Human behavior transformation is a complex process influenced by multiple factors. Therefore, theory-based interventions targeting multiple behavioral factors are needed to address the wide range of mechanisms relevant to the process of understanding HPV to receiving the 3 doses of the HPV vaccine. Promising results have been obtained from the school-based interventions for preventing cervical cancer in adolescents. This used the Health Belief Model (HBM) as a theoretical framework to examine the impact of intervention on HPV vaccination in 741 adolescents aged 16 years [18, 36]. The study design contained four elements: school-based setting, student-target participants, the Health Belief Model (HBM) and a 30 min face-to-face structured review delivered by school nurses. Results of this study demonstrated a significant improvement in the HPV vaccination rate from 52.5% before to 59% after the intervention, whereas no change was seen in the control group (60.9%). These findings are important as they suggest that making well-designed interventions can promote healthy behavior, such as receiving the HPV vaccine for cervical cancer prevention.

Alternatively, the results of DiClemente’s study, which made the vaccination free-of-charge for the intervention group so as to eliminate certain accessibility barriers in a clinical setting, did not show a statistically significant result [35]. Their findings suggest that objective factors, such as vaccine cost and accessibility, may not significantly contribute to poor vaccine uptake. In contrast, a low perceived susceptibility to the HPV infection may help explain the low vaccination rates observed in this study. Furthermore, both the limited sample size and inappropriate recruitment period that conflicted with adolescent’s school hours (9 am-5 pm) had a negative impact on HPV vaccination uptake. Finally, the 12-min media program was likely too short to affect the participants’ desire to receive the HPV vaccine. Thus, similar to the DiClemente’s trial, the current study will be conducted based on the IMB theory. At the same time, however, we will avoid the weaknesses of the above research, as the methodology section demonstrates.

In the current study, we will choose the female college students as the study participants because of their increasing sexual demand and the spread of HPV infection among them [20–22]. School-based interventions are employed as they have been proved suitable and effective in promoting the HPV vaccine in previous studies [16, 18]. In addition, the IMB model is used due to previously beneficial predictions and health behavior promotions across many health areas [35–37]. The Fisher’s recommendations have also been employed due to their usefulness in designing the IMB theory-based interventions to improve HPV vaccination rates in the future. Furthermore, the 7-day education via the mobile app is in line with the preferences of young people [23, 24]. Finally, taking the regional differences into account, our trial will set up seven sub-centers in accordance with the seven geographical divisions in China.

However, this study has potential limitations: First, there is no exact baseline data on vaccination rates to calculate an appropriate sample size, since the HPV vaccine has just been approved in China for just 3 years. Secondly, the short follow-up period of only 6 months and the unverified 7-day education method may also lead to measurement bias. Furthermore, the IMB theory-based questionnaire has not been fully validated among Chinese female college students.

To summarize, this is the first RCT to investigate theory-based interventions to improve human papillomavirus vaccination uptake among Chinese female college students. This multicenter RCT study will contribute to a growing research field which assesses the effectiveness of mobile-based, school-targeted and theoretically guided interventions for promoting HPV vaccination in adolescents.

## Data Availability

Not applicable.

## Appendix

## Abbreviations

CIs: Confidence Intervals
FDA: Food and Drug Administration
HPV: Human Papillomavirus
IMB: Information-Motivation-Behavioral skill
OR: Odds ratio
P: Probability
RCT: Randomized Controlled Trial
US: the United States
